## Methods and analysis

### Study design

This study is a prospective, randomized controlled study of capecitabine metronomic chemotherapy for mCRC patients reaching NED. All eligible individuals (240) will be randomly assigned to either a capecitabine metronomic chemotherapy group (*n* = 120) or a “watch-and-wait” group (*n* = 120). This study protocol has been approved by the Ethics Committee at Zhongshan Hospital of Traditional Chinese Medicine Affiliated to Guangzhou University of Chinese Medicine (No. 2021ZSZY-LLK-354) and registered in the Chinese Clinical Trial Registry (ChiCTR2100047149). All eligible participants will be required to sign an informed consent form prior to random grouping. The overall timeline and study procedures are outlined in Fig 1.

**Fig 1 pone.0320591.g001:**
[figure not shown]
Timeline and schedule of enrolment, interventions and assessments.

### Study subjects

All subjects will be recruited through posters at Zhongshan Hospital of Traditional Chinese Medicine Affiliated to Guangzhou University of Chinese Medicine.It will be conducted from December 2021 to December 2025.All subjects must be medically fit patients with mCRC advanced colon cancer who had achieved NED status after surgery or ablation, aged 18–80 years, and with an ECOG score of 0–1, and who have completed perioperative chemotherapy. Major exclusion criteria are multiple primary carcinoma patients; pregnant women; mentally ill patients; patients with other serious underlying diseases. Complete inclusion and exclusion criteria are outlined in Table 1.

**Table 1 pone.0320591.t001:** Study inclusion and exclusion criteria.

Inclusion criteria	Exclusion criteria
(1) Male or female aged 18–80 years.	(1) Patients diagnosed with more than one malignancy.
(2) Pathologically confirmed metastatic colorectal adenocarcinoma.	(2) Pregnant or lactating women.
(3) Contrast-enhanced CT or MRI of the chest and abdomen at the initial diagnosis, clinical stage IV colon cancer with liver and/or lung metastasis, and potentially curative R0 resection (including local therapy such as radiofrequency ablation) for the primary tumor and metastatic lesions, have completed perioperative chemotherapy, and achieved NED status on chest and abdomen CT or MRI within 4 weeks before enrollment.	(3) Patients with mental illness.
(4) ECOG score of 0–1.	(4) Combined with coronary heart disease, myocardial infarction, renal failure, pulmonary embolism and other diseases that may affect the survival of patients.
(5) There were no other underlying diseases affecting organ function.	(5) Patients with poor compliance can not cooperate with the treatment.
(6) Understand, be willing to give consent, and sign the written ICF prior to undergoing any study-specific procedure.	(6) There is a known deficiency of DPD, or Capecitabine intolerance.

Abbreviation: NED, no evidence of disease; ECOG, Eastern Co-operative Oncology Group; ICF, informed consent form; DPD, dihydropyrimidine dehydrogenase.

### Randomization, allocation and blinding

Eligible patients will be randomly assigned to either a watch-and-wait group or a capecitabine metronomic chemotherapy group in equal proportions via the random number table method. After the participants sign the informed consent form and complete the baseline assessment, the investigators will assign them a random number and assign the participants to the appropriate group. Participants will be informed that they have an equal chance of being assigned to the capecitabine metronomic chemotherapy group or to the watch-and-wait group. Subject assignment will be performed by an independent investigator in the clinical department who will not be involved in the evaluation of the results. The outcome assessors, data collectors, and statisticians will be blinded to the intervention assignment, but the patients participating in the study will not be blinded. Single blinding of the outcome assessors and data analysts will be maintained throughout the course of the study.The overall study design is illustrated in Fig 2.

**Fig 2 pone.0320591.g002:**
[figure not shown]
Flowchart of trial procedures.

### Intervention

The interventions studied will be implemented by attending physicians with at least 3 years of clinical experience in the Oncology Department at Zhongshan Affiliated Hospital, Guangzhou University of Chinese Medicine. Based on chemotherapy theory for metastatic colorectal cancer and previous randomized controlled trials, capecitabine chemotherapy process interventions will be developed under the consensus of colorectal cancer oncology experts. Prior to initiating the study, the clinical practitioner will receive specialized training to gain a comprehensive understanding of capecitabine metronomic chemotherapy, and to administer treatment in accordance with the specific requirements of the investigator’s manual. All eligible patients in both groups will have been diagnosed with stage IV colon cancer with hepatic and/or lung metastases, have potentially cured R0 resection of the primary tumor and metastatic lesion (including local treatments such as radiofrequency ablation), have completed perioperative chemotherapy, and have reached NED status on computed tomography (CT) or MRI within 4 weeks of enrollment. The study will be conducted over a 3-year period, with all treatments completed within the first 2 years. Follow-up will last for 12 months, beginning after the completion of the 24-month intervention period.

#### Capecitabine metronomic chemotherapy group.

All eligible patients will have been diagnosed with Stage IV mCRC according to the National Cancer Network (NCCN) colorectal cancer diagnosis and treatment guidelines. They also will have achieved NED after local treatment such as surgery or ablation and completed perioperative 6-month chemotherapy.

In the capecitabine metronomic chemotherapy group, after chemotherapy ends, patients will continue to take capecitabine (500 mg/m^2^ bid, uninterrupted) for 2 years, or until the disease progresses or the patient develops intolerable side effects. Retrieve the medication box and conduct a count of the remaining quantity to assess adherence, including instances of underdosing, overdosing, or loss of medication. During the trial period, each observation index will be re-visited every 3 months from postoperative intervals to determine whether there is any recurrent metastasis of the tumor. The follow-up will last for 1 year, and the observation indicators will be re-visited every 3 months.

#### Watch-and-wait group.

Eligible patients diagnosed with stage IV mCRC, both the primary tumor and the metastases, have achieved R0 resection (or complete destruction by ablation) and reached NED. After completing 6 months of perioperative chemotherapy, they will enter observational waiting.

The observation period will be 2 years, and the observation indicators will be re-visited every 3 months; the follow-up period will be 1 year. The enrolled patients will be reexamined with enhanced CT or MR every 3 months during the observation period and the follow-up period to determine whether there is any recurrence or metastasis of the tumor.

## Outcome

The primary endpoints disease-free survival (DFS) will be analyzed by using intention-to-treat (ITT) data set from randomization, stratified by preoperative chemotherapy, metastatic organs, number of metastases, lenght of previous systemic treatment (under 6 months, over 6 months), response to previous chemo: CR/PR or SD/PD. Secondary endpoints will include overall survival (OS), 1-year, 2- year and 3-year survival rate. The adverse reactions will be counted, and the bone marrow suppression rate and the incidence of digestive tract reactions will be used as safety evaluations.

### Primary outcomes

#### Disease-free survival (DFS).

Disease-free survival (DFS) refers to the survival time calculated from randomization without any locoregional progressive disease, distant metastasis, recurrence or secondary colorectal cancer. Death from any cause will also be considered an event for this endpoint.

The enrolled patients will be assessed every 3 months starting from the baseline (Month 0). At the same time, the enhanced CT or MR will be reexamined, and combined with the tumor marker level to evaluate the recurrence and metastasis of the tumor, to observe patient survival, and to calculate the DFS.

### Secondary outcome

#### Overall survival (OS).

Another primary outcome is patient overall survival (OS), which is the time from randomization to death from any cause. For patients who are lost to follow-up before death, the time of last follow-up will be calculated as the time of death.

Participating patients will be recorded from baseline (month 0), with visits every 3 months to document patient survival.

#### Survival rate (DFS and OS).

After visits at the time nodes specified in the trial, patient survival will be calculated at the time nodes of the 1^st^ year, 2^st^ year and the 3^nd^ year after randomization.

#### Safety.

All participants will undergo physical tests to evaluate their bodies before screening enrolling and after treatment. These tests will include the function of the heart, liver, kidneys, and other organs, including cardiac ultrasound, ECG, white blood cell count, hematocrit, platelets, aspartate aminotransferase/alanine transaminase, blood urea nitrogen, creatinine, γ-glutamyl transpeptidase, and erythrocyte sedimentation rate.

Adverse events (AEs) are any unexpected adverse conditions, symptoms, or sensations that occur in subjects throughout the trial period, whether or not they are associated with capecitabine treatment. AE will be graded using the Common Terminology Standard (CTCAE) 4.0.3 [20]. A serious adverse event (SAE) will be defined as any of grade 3, 4, or 5 adverse events. Each AE will be recorded on the case report form (CRF). SAE will be reported to the Competent Authorities and the Ethics Committee. Initiators must submit annual safety reports to Competent Authorities and Ethics Committees during clinical trials. At the same time, the incidence of bone marrow suppression and the incidence of gastrointestinal responses will be counted to assess the safety of capecitabine metronomic chemotherapy.

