### Sample size calculation

The sample size estimation was conducted using the Logrank Test, with disease-free survival (DFS) as the primary outcome measure. According to the JCOG0603 study, patients with mCRC who achieved NED status and received adjuvant chemotherapy had a 3-year DFS rate of 52.1% [7]. Based on the data from the phase II single-arm CAMCO trial [21], in conjunction with clinical expertise and expert opinions, We hypothesized that the 3-year DFS rate in the group receiving capecitabine metronomic chemotherapy would be 67.1%. We will need at least 119 participants in the intervention and control group, 238 participants in total (alpha = 0.05, power=0.90,). A drop-out of 5% is anticipated [22]. The sample size of this study was determined to be 240 participants, taking into account potential additional dropouts.

We calculated the sample size using the Lakatos method, which accounts for varying accrual times, dropout rates, and study length—critical factors for trials with survival endpoints like DFS. While the Freedman method is widely used for its simplicity, it assumes constant hazard ratios and patient compliance, which may not fully reflect the complexities of real-world trials. The Lakatos method [23], though more restrictive in its assumptions, offers a more realistic model for time-dependent variables and survival data, making it a better fit for our single-center study [24].

However, some assumptions of the Lakatos method may not hold in practice, potentially resulting in a wider confidence interval (CI) for the hazard ratio (HR). Although the Lakatos method may yield a smaller sample size compared to Freedman’s, we have carefully balanced statistical rigor with the feasibility of a single-center trial, given our available resources. To mitigate the risk of wide CIs, we will closely monitor accrual patterns and dropout rates throughout the study to ensure robust results.

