### Statistical analysis

The statistical analysis will use SPSS version 26.0 (IBM SPSS Statistics, New York, USA). All analysis will be based on the ITT dataset. Missing data will be supplemented with the principle of multiple interpolation. All statistical tests will use a two-side test, and *P* < 0.05 will be considered statistically significant for the difference being tested. The survival analysis will use the Kaplan-Meier method for one-factor survival, calculating the median disease DFS and OS of the two groups, and comparing the survival curves by the Logrank test. The χ² test will be used to analyze the counting data of adverse events (AEs). Additionally, the 95% confidence interval (CI) for the observed hazard ratio (HR) will be calculated at the end of the trial. *P* <0.05 will be considered statistically significant.

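### The adverse-event comparison runs past recurrence and past the end of capecitabine, which can dilute, and may mask, the toxicity difference between the arms

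*Protocol article*

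**What the plan says.** Four parts of the protocol article bear on this point.

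- **What is counted.** The Safety section defines AEs as those that "occur in subjects throughout the trial period, whether or not they are associated with capecitabine treatment", each recorded on the CRF. It adds that "the incidence of bone marrow suppression and the incidence of gastrointestinal responses will be counted to assess the safety of capecitabine metronomic chemotherapy".
- **How it is compared.** The Statistical analysis section assigns AE counts to a chi-square test and states: "All analysis will be based on the ITT dataset". It mentions no period split and no adjustment for exposure.
- **When exposure ends.** In the capecitabine arm, treatment continues "for 2 years, or until the disease progresses or the patient develops intolerable side effects".
- **How long patients are followed.** The Intervention section states: "Follow-up will last for 12 months, beginning after the completion of the 24-month intervention period". Overall survival is a secondary endpoint, "with visits every 3 months to document patient survival", so patients remain under observation after a DFS event.

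The article does not describe treatment after recurrence or its toxicity, and it gives no expected AE rate for either arm.

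**The concern.** The safety question is whether up to two years of metronomic capecitabine is tolerable compared with observation, in patients who have no evidence of disease. The count as written covers more than that. It takes in the 12 months after planned treatment ends and, for patients who recur, all the time after recurrence. If some of those patients receive further systemic treatment, its marrow and gastrointestinal toxicity falls on the two measures that the article names for safety, and is charged to the arm assigned at randomisation.

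Under the trial's own efficacy hypothesis, more control than capecitabine patients recur. The added toxicity then falls mainly on the control arm, and the better capecitabine works, the safer it looks. Safety is part of the stated objective, and the Conclusion expects the results to change guidelines, so a comparison biased towards no difference matters.

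**Working it through.** **Inputs from the article.** 120 patients per arm. 3-year DFS is 52.1% for control; for the other arm, "We hypothesized that the 3-year DFS rate in the group receiving capecitabine metronomic chemotherapy would be 67.1" percent. Tests are two-sided at 0.05. The article states no AE rate or AE power, so there is no AE figure to reproduce. The DFS sample size is a separate matter and is not used here.

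**Step 1: patients with a DFS event by 3 years.**
- Control: 120 × (1 − 0.521) = 57.5
- Capecitabine: 120 × (1 − 0.671) = 39.5

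These are upper limits for recurrence, because death from any cause and secondary colorectal cancer are also DFS events.

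**Step 2: time before and after the event (exponential DFS assumed).** The yearly hazard is λ = −ln(S)/3, which gives 0.2173 (control) and 0.1330 (capecitabine). Mean event-free time in 3 years is (1 − S)/λ.
- Control: 0.479/0.2173 = 2.204 years, leaving 0.796 years after the event (9.6 months)
- Capecitabine: 0.329/0.1330 = 2.474 years, leaving 0.526 years after the event (6.3 months)

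For 120 patients this is about 264 and 297 patient-years before the event, and 96 and 63 after it. Deaths reduce the last two figures.

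**Step 3: effect on the counted incidence.** Let b be the AE incidence without post-recurrence events, r the share with a DFS event, u the share of those treated afterwards, and q the AE probability on that treatment. Then

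counted incidence = 1 − (1 − b)(1 − r·u·q).

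All values of b, u and q below are assumptions.

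Worked example, b = 5% (control) and 20% (capecitabine), u = 0.8, q = 0.6:
- Control: 1 − 0.95 × (1 − 0.479 × 0.48) = 26.8%
- Capecitabine: 1 − 0.80 × (1 − 0.329 × 0.48) = 32.6%

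The 15-point difference becomes 5.8 points, and chi-square power with 120 per arm falls from about 94% to 16%. With u = 0.5 and q = 0.4 the counted rates are 14.1% and 25.3%, a difference of 11.2 points with power of about 59%.

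Range over u = 0.5 to 0.9 and q = 0.3 to 0.7:

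| True incidence (control vs capecitabine) | True difference | Counted difference | Power, true | Power, counted |
|---|---|---|---|---|
| 5% vs 15% | 10 points | +7.4 to −1.1 | 74% | 35% to 4% |
| 10% vs 30% | 20 points | 17.0 to 7.3 | 98% | 87% to 21% |
| 10% vs 50% | 40 points | 36.0 to 23.2 | near 100% | 95% or more |

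The difference shrinks in every row, from a tenth of it (40 to 36.0 points) to more than all of it (10 to −1.1 points).

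**Step 4: no DFS benefit.** Set r = 0.479 in both arms with b = 5% and 20%. The 15-point difference becomes 15 × (1 − 0.479 × 0.48) = 11.6 points, or 15 × (1 − 0.479 × 0.20) = 13.6 points in the milder case. Some dilution remains, but the part caused by unequal recurrence disappears.

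**The case against.** The case on the other side has real weight.

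- **The sentence defines what to collect.** Recording every AE to the end of the trial, whatever its cause, is right. A reader might infer that the wide definition is itself the mistake; it is not. The weakness arises where that count passes, without a window, into the stated between-arm test.
- **Capture after recurrence is uncertain.** The laboratory and organ-function tests are scheduled before enrolment and after treatment, and the later visits are described as documenting survival. How much marrow suppression after recurrence would be recorded cannot be told from the article. This limits the size, but the definition still admits those events.
- **An unseen analysis plan may set a window.** It may. But the article does more than stay silent: it fixes the period in its AE definition and states the ITT rule for all analyses. An analysis that follows the text includes post-recurrence AEs.
- **The mechanism is partly assumed.** A reader might infer that control patients will have more post-recurrence toxicity and that capecitabine's toxicity will be hidden. The documents do not support this as fact. The excess in controls follows only from the hypothesised DFS rates, and treatment after recurrence is not described. Deaths cannot be retreated and late events leave little time for it, so the figures above lean high. The plan also sets no power target for AEs; power serves here only as a yardstick.
- **A whole-period ITT count is legitimate.** It measures the total toxicity of each strategy, relapse treatment included. This stands, and is a reason to keep that table. It does not isolate the tolerability of capecitabine, which is the purpose the Safety section gives.

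Patients assigned to capecitabine who never take a dose would stay in the ITT denominator. That is minor, and the article gives no way to size it.

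**Conclusion.** The concern holds in a limited form. As written, AEs that arise after recurrence and after capecitabine has ended enter the comparison meant to judge its safety. If the DFS hypothesis is right, they enter more often in the control arm (up to about 57 against 39 of 120 patients at risk of contributing them), and the bias runs towards no difference. The toxicity contrast can be diluted and may be masked; that it will be masked is not shown. Over the assumed ranges the effect runs from a loss of about one tenth to full cancellation, and a 10% versus 50% difference keeps power of at least 95%. The direction rests on the plan's own hypothesised DFS rates and on some recurring patients receiving toxic treatment. The size rests wholly on AE and retreatment rates that the article does not give. The change is worth making because it is cheap and removes an avoidable bias from a stated objective.

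**What to change.** Keep recording all AEs to the end of the trial, and keep the whole-period ITT table as the strategy-level summary. Add, and name as the prespecified safety comparison, an analysis with an identical window in both arms: from randomisation to the earliest of recurrence, start of any subsequent anticancer treatment, or month 24 plus a fixed lag (for example 30 days).

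Within that window, report marrow suppression and gastrointestinal reactions per patient-month or as time to first event, because a cut at recurrence leaves unequal time at risk. Over 24 months, on the plan's DFS rates and exponential times, the 2-year event shares are 35.3% and 23.4%. Event-free time is then 120 × 0.3525/0.2173 ≈ 195 patient-years for control and 120 × 0.2336/0.1330 ≈ 211 for capecitabine. List later AEs separately, with the treatment being received at the time.

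The cost is a paragraph of wording and one more CRF item, the start date of subsequent treatment. Three drawbacks should be stated openly: the cut is at an outcome-related event, later toxicity leaves the main comparison, and the capecitabine contrast may look less favourable than under whole-period counting.

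### Serious adverse events are defined by CTCAE grade instead of seriousness, and adverse events are worded as unexpected only, so events are misclassified for reporting and counting

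*Protocol article*

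**What the plan says.** Both definitions stand in the Safety section of the protocol article, under Secondary outcome.

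- **Adverse event:** "Adverse events (AEs) are any unexpected adverse conditions, symptoms, or sensations that occur in subjects throughout the trial period", and this applies "whether or not they are associated with capecitabine treatment".
- **Grading:** "AE will be graded using the Common Terminology Standard (CTCAE) 4.0.3".
- **Serious adverse event:** "A serious adverse event (SAE) will be defined as any of grade 3, 4, or 5 adverse events".
- **Reporting:** "SAE will be reported to the Competent Authorities and the Ethics Committee". In addition, "Initiators must submit annual safety reports to Competent Authorities and Ethics Committees during clinical trials". Every AE, at any grade, goes on the case report form.

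The Outcome section says that adverse reactions will be counted and that "the bone marrow suppression rate and the incidence of digestive tract reactions will be used as safety evaluations". The Safety section repeats that these two classes of toxicity will be counted. The Statistical analysis section compares AE counts with a chi-square test.

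**The concern.** Severity and seriousness are different properties of an event. A CTCAE grade says how intense the event is. Seriousness says what it led to: death, threat to life, hospitalisation or its prolongation, persistent disability, congenital anomaly, or another medically important outcome. The plan defines the second by the first and then attaches external reporting to the result. Serious events of low grade can therefore miss the reporting route, and harmless high-grade laboratory findings can fill it.

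The word *unexpected* adds a second problem. The known reactions to a chemotherapy drug are expected. A definition that covers only unexpected events leaves them out of the AE total. Because SAEs are a subset of AEs, it leaves them out of the SAE total too.

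Safety is half of the trial's stated aim and adverse reactions are a secondary outcome, so the classification matters for participant protection and for the safety comparison. The Quality control section also makes SAE reporting part of the three-monthly independent audit, which covers whether to stop the study early. A wrongly drawn set of SAEs would reach that oversight.

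**Working it through.** No arithmetic applies: neither definition depends on a rate, an effect size or a sample size, and the article gives no toxicity figures. The check applies the written rules to typical events and compares the result with outcome-based seriousness.

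| Event | AE as written? | Reported as SAE as written? | Serious by outcome? |
|---|---|---|---|
| A. Grade 1–2, not anticipated, leads to hospitalisation | yes | **no** | yes |
| B. Grade 3 laboratory value, not anticipated, no symptoms or consequences | yes | **yes** | no |
| C. Grade 3–5, not anticipated, leads to hospitalisation | yes | yes | yes |
| D. Grade 3–5, anticipated toxicity, leads to hospitalisation | **no**, read literally | **no**, read literally | yes |
| E. Grade 1–2, anticipated toxicity, no serious outcome | **no**, read literally | no | no, but it belongs in the AE count |

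**Rows A and B** follow from the SAE rule alone. They remain wrong however *unexpected* is read. Row B is a practical possibility because the Safety section lists white cells, platelets, transaminases, creatinine and γ-glutamyl transpeptidase among the tests for all participants.

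**Row C** is the only case in the table where the written rules and outcome-based seriousness agree that an event is serious.

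**Rows D and E** depend on the literal reading of *unexpected*. The clause about association with capecitabine removes a causality limit but does not remove an expectedness limit. For bone marrow suppression and gastrointestinal reactions the omission is made good in part, since the Outcome and Safety sections have them counted on their own account. They would still be missing from the overall AE total and, at grade 3–5, from SAE status. Other anticipated toxicities have no such separate named count.

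**Direction.** One arm takes capecitabine for up to two years and the other is observed. Omitting anticipated drug reactions would therefore lower the count mainly in the capecitabine arm, and the error would favour capecitabine.

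**The case against.** The strongest defence concerns the word *unexpected*. The clause on association with capecitabine has the scope of an ordinary broad AE definition, so the word may simply be loose English for untoward. The Outcome section says adverse reactions will be counted without that qualifier, and the two toxicities named as safety evaluations are counted whatever the definition says. This largely stands. It reduces the AE half to a wording fault that exposes overall totals, other anticipated toxicities and SAE status.

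Three stronger conclusions might be inferred, and the article does not support them.

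- *Low-grade serious events go unreported altogether.* Every AE as defined goes on the case report form at any grade, and annual safety reports are required, although their content is not described. What is lost is reporting as an SAE.
- *The under-count falls in the capecitabine arm only.* Both arms enter after six months of perioperative chemotherapy, so anticipated residual effects can occur in controls too. Mainly is supportable; only is not.
- *The AE definition cancels the safety endpoint.* It conflicts in wording with the two named evaluations, but it does not remove them.

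It can also be said that reporting symptom-free grade 3 values errs on the cautious side, that comparisons by CTCAE grade do not depend on the SAE label, and that DFS, OS and the sample size are untouched. All of this is correct. It limits the reach of the point but does not answer row A, where nothing in the article supplies the missing criterion.

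**Conclusion.** Wrong as written. The grade-only SAE definition is an explicit rule, not a detail left to a fuller document, and no charitable reading repairs it. Its effect is confined to two groups: grade 1–2 events with a serious outcome, which miss SAE reporting, and non-serious grade 3 events, which enter it.

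The AE wording is a secondary fault. Its effect depends on how literally site staff apply one word, and it is limited to other anticipated toxicities and to overall AE and SAE totals, mainly in the capecitabine arm.

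Neither effect can be sized from the article, which gives no toxicity rates and no information on how closely grade tracks outcome in practice. The conclusion assumes that the definitions are applied as printed and that the full protocol, which is not shown, does not replace them. The case for acting now rests on the SAE definition as a matter of participant safety reporting. The primary efficacy analysis is not affected.

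**What to change.** 1. Define an SAE by the standard outcome criteria: death, threat to life, hospitalisation or its prolongation, persistent disability, congenital anomaly, or another medically important event.
2. Keep grade 3–5 AEs as a separate severity summary under its own name.
3. In the AE definition, replace *unexpected* with *untoward*, and state that it covers events whether expected or not and related or not.
4. Re-check the classification of events already recorded. The Trial status section says that the trial has been recruiting since 31 December 2021, so events may already have been classified under the current wording. Also check whether anticipated toxicities were left off the form.

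The cost is two reworded definitions, one seriousness field on the case report form and a small retrospective check. The sample size, the visit plan and the primary analysis do not change.
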